### Efficacy outcome measures

Outcomes and endpoints are the same for both the placebo-controlled and OLE phases of the trial.

#### Primary efficacy outcome measures

##### Change of D1 domain of motor function under tamoxifen compared to placebo in ambulant patients

In group A, which includes only ambulant patients, the primary efficacy outcome is the change of motor function measured by the MFM. MFM is a commonly used assessment in patients with DMD that has been validated in Lyon, France [29–31]. The test measures all dimensions of the motor function by evaluating standing and transfer (D1 domain), axial and proximal (D2 domain), and distal motor function (D3 domain). The reliability of the MFM has been examined in several studies. It is described as being sensitive to treatment response [32] and to disease progression even within as short a period as 3 months [33, 34]. The D1 domain of the MFM, assessing standing and transfer, was shown to be the most powerful parameter to detect clinical decline compared to D2 and D3 domains [35].

##### Change of D2 domain of motor function under tamoxifen compared to placebo in nonambulant patients

Since the D1 domain remains around 0% in patients who have lost ambulation it cannot be applied to monitor disease progression or treatment response in nonambulant patients. In contrast, the D2 and D3 domains are more suitable for nonambulant patients as these assess the retained upper limb functions [29, 32, 33]. The D2 domain in particular was shown to be informative, with a decrease of 9.4% per year in nonambulant patients [33]. Therefore, the D2 domain, assessing axial and proximal motor function, is defined as the primary endpoint for the group B (nonambulant) population of the study.

#### Secondary efficacy outcome measures

##### Change of motor function measured by the MFM total score, its D2 and D3 domains, NSAA and PUL under tamoxifen compared to placebo

The total MFM and also its D2 and D3 domains are defined as secondary endpoints, giving complete information about all three dimensions of the motor function including axial, proximal and distal motor function. The NSAA is another commonly used and validated test to measure motor function in ambulant children with DMD [36, 37]. The test can be used in children from the age of 4 years [38]; moreover, a revised version of NSAA was recently proposed to be used in patients above 3 years of age [39]. The functional testing of the upper limbs is a reliable parameter both in ambulant and nonambulant patients, but its application is especially meaningful in patients who have lost ambulation [40].

##### Change in TFT measured by 6MWT, 10MWT and time to rise from the floor under tamoxifen compared to placebo

TFT are useful clinical assessments in ambulant patients since they provide important information about the patient’s endurance. The 6MWT has especially been shown to be a good surrogate marker of disease progression as it independently predicts loss of ambulation [41–44]. A walking distance of <350 m in the 6MWT is considered a strong predictor of clinical decline [41, 42, 45, 46]. TFT of the study will include 6MWT, 10MWT and time to rise from the floor.

##### Change in QMT measured by grip force under tamoxifen compared to placebo

To measure the change in isometric muscle strength under treatment compared to placebo QMT using grip force measured by a handheld dynamometer will be performed [47].

##### Change in qMRI measurement of thigh muscles using FF and T2 under tamoxifen compared to placebo

qMRI is considered to be the most sensitive biomarker in patients with DMD. It assesses disease-related tissue changes including fat replacement (muscle FF), muscle edema and inflammation (T2). It objectively correlates with functional outcome measures in detecting clinical decline [48–51], reliably shows subclinical changes, and can even predict loss of ambulation [52, 53]. In this study, qMRI of all thigh muscles (flexors, extensors, and adductors) will be performed using FF and T2.

#### Patient-reported outcome measures

PARS-III is a parent-reported assessment that gives useful information about the psychosocial adjustment of a child. The test has been used in several chronic diseases and described as reliable and valid in patients with DMD [54]. The PARS-III will be performed throughout the study (at baseline, at weeks 24, 48, and in the OLE phase at weeks 72 and 96).

#### Safety outcome measures

The following safety assessments are performed at each visit: blood pressure, heart rate, weight, height, Wells score for deep vein thrombosis and electrocardiogram. Furthermore, the following safety laboratory assessments will be performed by routine testing at each visit: CK, gamma GT, total bilirubin, urea, AP, creatinine, electrolytes, triglycerides and full blood count including erythrocytes, leukocytes (with a differential), platelets, hemoglobin, hematocrit, and absolute neutrophil count. Tanner staging, ophthalmological examination, laboratory sex hormone concentrations (LH, FSH, testosterone, SHBG), and AFP will be monitored at baseline, at weeks 24 and 48, and also in the OLE phase at weeks 72 und 96. The cognitive function in the study population will be monitored by means of the RCPM test at baseline, at week 48, and also at week 96 in the OLE phase. RCPM is a validated, easy-to-perform, language-independent assessment which can be used in patients with severe motor or cognitive impairment. Normative values are available for the patient age group. RCPM has classically been used to measure global cognitive performance and has been used in DMD [55]. In selected sites, x-ray bone age determination (examination of the left hand) and lumbar spinal bone density measured by DEXA will be performed at baseline, at week 48, and at week 96 in the OLE phase.

#### Further outcomes of interest

The following markers of tamoxifen metabolism will also be assessed. Cyp2D6 and Cyp3A4 are the enzymes involved in the degradation of tamoxifen, while endoxifen and 4-OH-tamoxifen are considered as potential active metabolites. To examine muscle dystrophy biomarkers, TNF, TGFβ, IL-1β, IL-6, platelet-derived growth factor-B, IGF1, fibroblast growth factor 21, connective tissue growth factor, osteopontin, tissue inhibitor of metalloproteinases 1, matrix metalloproteinase (MMP)-2, and MMP-9 will be analyzed.

#### Objectives of the OLE phase of the main study

Outcome measures are the same for both the placebo-controlled and OLE phases of the trial. The goal of the OLE part is to test if earlier initiation of tamoxifen treatment (verum arm of the double-blind study) can reduce disease progression more efficiently. Therefore, disease progression during the OLE phase will be compared between both OLE treatment arms. A further aim is to obtain more safety and efficacy information.

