## Methods/design

### Study design

This is an investigator-initiated, multicenter, randomized, double-blind, placebo-controlled phase III efficacy and safety trial in patients with DMD. This part of the study is conducted over 48 weeks. The two treatment arms include tamoxifen (verum) and placebo (control). We plan to enroll at least 71 ambulant patients aged between 6.5 and 12 years (group A) and 16–20 nonambulant patients aged between 10 and 16 years (group B) at multiple European sites (Belgium, France, Germany, Netherlands, Spain, Switzerland, Turkey, and the United Kingdom). After completion of the double-blind phase, all participants will be offered the option of taking part in an open-label extension (OLE) trial of the main study. In this part, all patients will receive tamoxifen for 48 weeks.

The trial was approved by the local ethics committee (ethics committee of both Basel cantons, 2017–01708), the National Swiss Drug Agency (Swissmedic, 2018DR3068), the European Union Drug Regulating Authorities Clinical Trials (EudraCT 2017–004554-42), and the European Union Drug Regulating Authorities Pharmacovigilance (EudraVigilance). The study was registered at ClinicalTrials.gov (NCT03354039) and at the Swiss National Clinical Trials Portal (SNCTP000002387) prior to recruitment. The SPIRIT flow chart showing the main study design is seen in Fig. 1, while Fig. 2 represents the study design of the OLE phase. The Recommendations for Interventional Trials (SPIRIT) checklist on which the study protocol is based is presented as Additional file 1.

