### Sample size estimation

Sample size estimation was performed for the ambulant patients to allow the identification of a significant difference in the D1 domain between the two treatment groups (verum versus placebo). A type I error rate of α = 0.05 was used and the power was set at 1 – β = 0.8. The sample size estimation was based on clinical data from patients in the placebo arm of the Treatment with L-citrulline and metformin in Duchenne muscular dystrophy (DMD02) study [52]. The mean change in D1 domain of these patients was 9.1% during 25 weeks while, previously, an annual D1 decline of 17.2% was reported in ambulant DMD patients [32].

A semiparametric method was performed to account both nonparametrically for the available dataset and parametrically for the treatment shift. Each sample size, *n*i = 1, ..., 50 = 30, ..., 1500, was evaluated by drawing 99 times an individual dataset of size *n*i from the pilot study dataset. Here, *n*i patients were sampled with replacement from a pilot dataset. For each sample, the average disease progression (mean) between baseline and follow-up was estimated. For patients assigned to placebo, the follow-up measurement of the pilot data was used as the expected follow-up measurement. In patients assigned to tamoxifen, the follow-up measurement was recalculated by adding the treatment effect. An analysis of covariance (ANCOVA) model was used to assess whether the D1 domain significantly differed between the two treatment groups after 48 weeks when adjusting for baseline values. Based on the assumption that tamoxifen reduces the mean decrease of D1 by 50% within 1 year, 79 patients should be screened in group A of the study population. A reduction of 50% corresponds to an average loss of 4.5 points in the D1 subscore under verum compared to a loss of 9 points under placebo. Assuming a screening failure rate of 10% and a drop-out rate of 15%, 79 screened patients would result in 71 randomized patients to ensure 60 evaluable patients in total.

Sample size estimation for the nonambulant patient group was based on practical considerations. Group B does not constitute our main study population and is included to obtain some additional safety and efficacy data. Therefore, statistical power calculations were omitted in this population.

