### Statistical analysis

#### Primary analysis

The primary analysis will be based on the D1 domain of the MFM in ambulant patients. For both groups A and B, two analysis sets will be built. The full analysis set will include all patients who had at least one follow-up measurement at week 24 or later. The per-protocol set will include all patients from the full analysis set who had the 1-year follow-up visit, and who had a drug compliance of 70–100%. The analysis will be done on the intention-to-treat principle. The measurement at randomization (week 0) will be considered as the baseline and the measurement at week 48 as the primary endpoint. An ANCOVA approach will be used: D1 at 48 weeks will be modeled using a linear regression model including D1 at baseline and treatment groups (verum versus placebo) as predictors in the model. Medication with glucocorticoids will be included as a covariable. Since D1 can be performed only in ambulant patients, this patient group will be used for the primary analysis. The model will be controlled by checking the model assumptions and by inspecting the residuals and leverages.

A following sensitivity analysis will be done to support the main analysis: concomitant use of CYP2D6 inhibitors in the treatment arm as an interaction term, glucocorticoid use in the treatment arm as an interaction term, exclusion of adjustment for glucocorticoid use, exclusion of multiple imputations (the last observation available at least 24 weeks after randomization will be imputed for missing values), inclusion of all measurements at weeks 0, 12, 24, 36, and 48 in a mixed -effects model, and repetition of the analysis on the per-protocol dataset.

For further efficacy analysis, the previously described ANCOVA approach (based on the primary outcome measure) will be performed also for the OLE phase.

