This multicenter, randomized, double-blind and placebo-controlled trial investigates whether tamoxifen can reduce disease progression by at least 50% compared to placebo in 6.5–12-year-old ambulant (group A) DMD patients. The goal of the OLE part is to test if earlier initiation of tamoxifen treatment (patients of the verum arm of the randomized controlled trial phase of this study) can reduce disease progression more efficiently than later treatment onset. Therefore, disease progression during the OLE phase will be compared between both OLE treatment arms. Finally, we also address the question whether tamoxifen can reduce clinical decline in 10–16-year-old nonambulant DMD patients who are not receiving steroids (group B). The inclusion of these patients was highly encouraged by the European Medicines Agency (EMA) in order to obtain more data on safety and efficacy in this patient group, even if statistical significance is not to be expected. The design of this trial, including duration, inclusion and exclusion criteria, efficacy and safety endpoints and statistical analysis regarding sample size and final analysis, have been discussed in detail and agreed with external opinions (Committee for Medicinal Products for Human Use (CHMP) of the EMA, Advisory Committee for Therapeutics (TACT) of Translational Research in Europe for the Assessment and Treatment of Neuromuscular Disease (TREAT-NMD), Sandoz, who are providing the investigational medicinal product, national competent authorities, and responsible ethical committees of the participating countries).

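### The extension asks whether starting tamoxifen earlier is better, but the comparison it states leaves out any gain already made by week 48

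*Protocol article*

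**What the plan says.** The section Objectives of the OLE phase of the main study sets the aim of testing earlier initiation and draws from it that "disease progression during the OLE phase will be compared between both OLE treatment arms". The Discussion repeats both steps. It gives the aim as "The goal of the OLE part is to test if earlier initiation of tamoxifen treatment", meaning the boys from the verum arm, "can reduce disease progression more efficiently than later treatment onset", and again derives the OLE-phase comparison from it.

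Study design says of the extension: "In this part, all patients will receive tamoxifen for 48 weeks". Study procedure places its first visit at week 48 and its last efficacy assessment at week 96.

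The only model given for the extension is in Primary analysis: "the previously described ANCOVA approach (based on the primary outcome measure) will be performed also for the OLE phase". The model referred to was defined for the double-blind phase: "The measurement at randomization (week 0) will be considered as the baseline and the measurement at week 48 as the primary endpoint". No baseline week or endpoint week is named for the OLE.

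**The concern.** Boys randomised to tamoxifen have a 48-week head start. If that is worth something lasting, the worth is the gap between the arms when the extension opens, carried forward to week 96. A comparison of what happens only between weeks 48 and 96 starts both arms afresh and removes that gap.

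A result near zero could then be read as showing that the time of starting does not matter, when it would also be the expected result of a lasting benefit. The protocol makes this case the relevant one. Under Safety assessments the OLE is ended if the primary endpoint is not significant, so it runs to its planned end only after a difference at week 48 has been shown.

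**Working it through.** **Inputs from the protocol.** Sample size estimation assumes an "average loss of 4.5 points in the D1 subscore under verum compared to a loss of 9 points under placebo", and states: "A type I error rate of α = 0.05 was used and the power was set at 1 – β = 0.8". It plans 79 screened, 71 randomised and 60 evaluable boys, with 10% screening failure and 15% drop-out. Allocation is 1:1. It also cites observed D1 declines of 9.1% in 25 weeks and 17.2% per year.

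**The plan's own figures.** 60 / (1 − 0.15) = 70.6, rounded up to 71. 71 / (1 − 0.10) = 78.9, rounded up to 79. Both reproduce. The 60 comes from resampling a pilot dataset that is not shown, so it cannot be recomputed. No figure is given for the OLE comparison.

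**The contrast in means.** Let D48 and D96 be the delayed-start minus early-start mean loss of D1 since randomisation, at weeks 48 and 96. The OLE-phase contrast is

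D(OLE) = D96 − D48.

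It therefore subtracts the gain present at week 48. With D48 = 9 − 4.5 = 4.5:

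| Course in the OLE (assumed) | OLE loss, early / delayed | D(OLE) | Loss weeks 0–96, early / delayed | D96 |
|---|---|---|---|---|
| Parallel decline | 4.5 / 4.5 | 0 | 9 / 13.5 | 4.5 |
| Early start also slows later decline | 3.0 / 4.5 | 1.5 | 7.5 / 13.5 | 6.0 |
| Delayed arm catches up fully | 4.5 / 0 | −4.5 | 9 / 9 | 0 |

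The first row does not depend on the size of the effect. If the 48-week placebo loss is 17.2 (the annual figure taken as it stands) or 9.1 × 48 / 25 = 17.5, and tamoxifen halves it, D96 is 8.6 to 8.7 and D(OLE) is still 0.

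**Illustrative rejection rates.** The protocol gives no SD. The one implied by 30 per arm, a difference of 4.5, two-sided 0.05 (sidedness is not stated) and power 0.80 is 4.5 / [(1.960 + 0.842) × √(2/30)] = 6.22. The simulation used 4000 trials with 30 per arm, a 48-week change SD of 6.22 and no OLE drop-out. It was run with measurement-error SD 2 and baseline SD 15, and again with 4 and 10. Under parallel decline:

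- Change from week 48 to week 96: mean difference 0.0, rejection rate 0.046 to 0.048.
- ANCOVA of week 96 on the week 48 value: 0.06 to 0.59 points (regression to the mean), rejection rate 0.048 to 0.064.
- ANCOVA of week 96 on the week 0 value: 4.5 points, rejection rate 0.53 to 0.73.

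With measurement-error SD 2 and baseline SD 15, the second row of the table gave a rejection rate of about 0.16 for the OLE-phase change and 0.79 for week 96 on week 0. The third row gave 0.79 for the OLE-phase change, in favour of delayed start. With 25 per arm, the week 96 analysis under parallel decline rejected in 43% of trials at a change SD of 6.1 and in 25% at 8.5.

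**The case against.** The strongest reply is that no passage names a week 48 baseline. The one model in the text has week 0 as its baseline, and carrying it over with a week 96 endpoint would be essentially the right analysis. On that view the objectives sentence is loose wording, and the exact weeks belong in the statistical analysis plan, which is not shown and may settle the matter. This stands in part. A reader might infer that the plan fixes an ANCOVA from week 48; it does not, and that is only one reading. But the comparison during the OLE phase is stated twice, each time as the consequence of the aim. A week 0 to week 96 model is not that comparison, so the sections conflict whichever reading was meant.

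A reader might also infer that the stated comparison must show no difference whenever early start helps. That goes too far. The protocol nowhere assumes equal decline in the two arms after week 48. It cites a low walking distance and a low D1 as predictors of decline and of loss of ambulation, so boys who enter the extension worse may decline faster. The contrast would then pick up the difference in later rates, though not the gap already present.

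Progression during the OLE does bear on whether a gap shown at week 48 holds, widens or closes. That is a reason to keep it as supporting information. Full catch-up, where the contrast favours delayed start, shows how it can mislead taken alone. It is not an example of a lasting benefit being missed.

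Finally, the rejection rates rest on SDs and numbers that the protocol does not give.

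**Conclusion.** The point holds in this form: the comparison stated in the objectives and the Discussion does not answer the question set there, and the statistical section does not repair this because it names no OLE baseline or endpoint week. On the protocol's own losses, a preserved gain followed by parallel decline gives 0 points in the stated contrast and 4.5 points from randomisation to week 96. These two figures need no SD. They do rest on the assumption of a 4.5 point loss in both arms during the OLE; if later rates differ, the contrast shows only that part of the benefit (1.5 of 6.0 points in the example).

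The documents do not support saying that a week 48 ANCOVA is the planned model or that a null result is certain. The power of 0.25 to 0.73 for the week 96 analysis under parallel decline is an illustrative range only; it depends on the assumed SDs and numbers per arm and models no OLE attrition. This is a secondary analysis and the primary one is untouched, but it is the extension's named efficacy aim and should be corrected.

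**What to change.** State the early-versus-delayed contrast in the objectives, and use the same wording in Primary analysis and the Discussion: D1 at week 96 by randomised arm, from an ANCOVA with week 0 D1 and glucocorticoid use as covariates, reported beside the week 48 difference. Keep the week 48 to 96 change as supportive only, to describe whether the courses are parallel, converging or diverging.

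The cost is a rewording. The physiotherapy assessment is already scheduled at week 96, so no visit is added. The price lies in missing data. OLE entry is optional and requires completion of the main study, and boys who decline have only a week 60 visit without physiotherapy assessment, hence no D1 after week 48. The week 96 estimate by randomised arm therefore rests on assumptions about these boys. The text should state the assumptions and add a sensitivity analysis that varies them.

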### Randomization scheme

At the baseline visit patients will be randomly assigned either to the active treatment or the control group. Stratification will be performed according to glucocorticoid use into the three strata of continuous user, intermittent user, and no user of glucocorticoid. The randomization procedure will be implemented by the Clinical Trial Unit (CTU) of the University Hospital Basel into a web-based randomization service tool for multicenter trials (randomizer.at), provided by the Institute for Medical Informatics, Statistics and Documentation of the Medical University Graz. It will include a standard minimization algorithm which will ensure that the treatment groups are balanced within each stratum. To avoid predictable alternation of treatment allocation, and thus potential loss of allocation concealment, patients will be allocated with a probability of 80% to the treatment group to minimize the difference between the groups within the patient’s stratum.

### Sample size estimation

Sample size estimation was performed for the ambulant patients to allow the identification of a significant difference in the D1 domain between the two treatment groups (verum versus placebo). A type I error rate of α = 0.05 was used and the power was set at 1 – β = 0.8. The sample size estimation was based on clinical data from patients in the placebo arm of the Treatment with L-citrulline and metformin in Duchenne muscular dystrophy (DMD02) study [52]. The mean change in D1 domain of these patients was 9.1% during 25 weeks while, previously, an annual D1 decline of 17.2% was reported in ambulant DMD patients [32].

A semiparametric method was performed to account both nonparametrically for the available dataset and parametrically for the treatment shift. Each sample size, *n*i = 1, ..., 50 = 30, ..., 1500, was evaluated by drawing 99 times an individual dataset of size *n*i from the pilot study dataset. Here, *n*i patients were sampled with replacement from a pilot dataset. For each sample, the average disease progression (mean) between baseline and follow-up was estimated. For patients assigned to placebo, the follow-up measurement of the pilot data was used as the expected follow-up measurement. In patients assigned to tamoxifen, the follow-up measurement was recalculated by adding the treatment effect. An analysis of covariance (ANCOVA) model was used to assess whether the D1 domain significantly differed between the two treatment groups after 48 weeks when adjusting for baseline values. Based on the assumption that tamoxifen reduces the mean decrease of D1 by 50% within 1 year, 79 patients should be screened in group A of the study population. A reduction of 50% corresponds to an average loss of 4.5 points in the D1 subscore under verum compared to a loss of 9 points under placebo. Assuming a screening failure rate of 10% and a drop-out rate of 15%, 79 screened patients would result in 71 randomized patients to ensure 60 evaluable patients in total.

Sample size estimation for the nonambulant patient group was based on practical considerations. Group B does not constitute our main study population and is included to obtain some additional safety and efficacy data. Therefore, statistical power calculations were omitted in this population.

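### The sample size calculation presents a 25-week pilot decline in D1 as the one-year decline, so the stated 80% power is not established for the week-48 primary comparison

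*Protocol article*

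**What the plan says.** All of the planning figures stand in the section on sample size estimation of the protocol article.

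- **Pilot data.** The calculation rests on the placebo arm of an earlier trial in the same disease. The section reports: "The mean change in D1 domain of these patients was 9.1% during 25 weeks while, previously, an annual D1 decline of 17.2% was reported".
- **Simulation.** Datasets were resampled from the pilot. For placebo patients, "the follow-up measurement of the pilot data was used as the expected follow-up measurement". For tamoxifen patients the treatment effect was added to that value. No conversion from 25 to 48 weeks is described, and no SD is given.
- **Comparison.** ANCOVA was used to test whether D1 "significantly differed between the two treatment groups after 48 weeks when adjusting for baseline values".
- **Effect.** Tamoxifen is assumed to halve the mean D1 decrease within one year, which the section equates to "an average loss of 4.5 points in the D1 subscore under verum compared to a loss of 9 points under placebo".
- **Error rates and size.** "A type I error rate of α = 0.05 was used" and "the power was set at 1 – β = 0.8". The result is 60 evaluable, 71 randomised and 79 screened patients.

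The primary analysis section then fixes week 48 as the time point of the primary endpoint.

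**The concern.** The planned placebo loss is tied to one year, but its size is that of a loss over about half a year. The annual rate cited beside it is nearly twice as large. If the pilot follow-up values entered the simulation unchanged, both the mean difference and the outcome spread describe roughly 25 weeks, while the result is labelled as a 48-week comparison.

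The two consequences pull in opposite directions. Over a longer interval, a true 50% slowing would give a larger difference, which raises power. Differences between patients in rate of decline would also widen the outcome spread, which lowers it. The stated 80% is therefore neither a lower nor an upper bound.

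This affects how the result is read. The discussion gives the aim as a reduction in progression of at least 50%, and under the safety assessments a nonsignificant primary result ends the extension phase. Readers of a null result need to know what difference the trial could have detected at week 48.

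**Working it through.** **Inputs from the protocol article.** Pilot placebo loss 9.1 over 25 weeks; cited annual loss 17.2; planned losses 9 and 4.5; α = 0.05; power 0.80; allocation 1:1; 60 evaluable; screening failure 10%; drop-out 15%. The D1 percentages are read as points on the D1 scale, as the section itself does.

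**Assumptions of this check.** Two-sided α (sidedness is not stated), 30 evaluable per arm, linear decline for the conversions.

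**1. The plan's own cascade.** 79 × 0.90 = 71.1 and 71 × 0.85 = 60.4. The figures 79, 71 and 60 reproduce. The 60 itself cannot be reproduced, because it comes from pilot data that are not shown.

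**2. Time scale of the 9 points.**

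- Annual rate at 25 weeks: 17.2 × 25/52 = 8.3
- Annual rate at 48 weeks: 17.2 × 48/52 = 15.9
- Pilot rate at 48 weeks: 9.1 × 48/25 = 17.5

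The 9 points agree with both sources at 25 weeks and with neither at 48 weeks.

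**3. The 50% effect at week 48.** 15.9/2 = 7.9 and 17.5/2 = 8.7 points. Conversely, 4.5/15.9 = 28% and 4.5/17.5 = 26%, so 4.5 points is a reduction of 26 to 28% of the decline that the cited rates imply.

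**4. Implied pilot SD.** The noncentrality is δ / (SD × √(2/n per arm)), tested on a t distribution with 2n − 3 degrees of freedom.

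- If power is exactly 80% at 60 patients (30 per arm, 57 df) with δ = 4.5, SD = 6.1.
- The section describes 50 candidate sizes from 30 to 1500. With equal steps the spacing is (1500 − 30)/49 = 30, so 60 is the second candidate. Choosing 60 then shows only that 30 was too few. An SD giving exactly 80% at 30 patients (15 per arm) is 4.2, and with that SD the power at 60 is 98%.

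The implied residual SD is therefore about 4.2 to 6.1. Each size was evaluated with 99 draws, so the Monte Carlo standard error at 80% is √(0.8 × 0.2/99) = 4 percentage points.

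**5. Power at week 48 with 30 per arm.** The document gives no 48-week SD. Growth by √(48/25) = 1.39 (square root of time) up to 48/25 = 1.92 (proportional to time) is assumed.

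| Pilot SD | Growth | 48-week SD | δ = 4.5 | δ = 7.9 | δ = 8.7 |
|---|---|---|---|---|---|
| 4.2 | ×1.39 | 5.9 | 83% | >99% | >99% |
| 4.2 | ×1.92 | 8.1 | 56% | 96% | 98% |
| 6.1 | ×1.39 | 8.5 | 52% | 95% | 98% |
| 6.1 | ×1.92 | 11.7 | 31% | 73% | 81% |

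With no growth in the SD, power for 4.5 points is 80% (SD 6.1) to 98% (SD 4.2), and above 99% for 7.9 to 8.7 points.

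**The case against.** **Nine points may suit this population.** Group A must walk at least 350 m, have D1 above 40% and be on stable glucocorticoids. The article calls a distance below 350 m a strong predictor of decline, and its discussion links a yearly loss of 17.2% to loss of ambulation. Carrying 17.2 over to boys selected above those thresholds may overstate their decline. This is a reasonable defence of 9 points as a value. It is not the reason the article gives: 9 points is simply equated with a one-year halving, and nothing calls it cautious. Caution about the mean would also leave the time basis of the spread open.

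**The low power figures combine premises that fit poorly.** The 31% pairs half the pilot rate of decline with a spread that grows as if the pilot rate continued. If slope differences shrink along with the mean, the growth is 1.92 × 0.5, or about 1, and power stays near 80%. Measurement error that does not grow with time would also keep the factor below 1.92. This stands, and it is why 31% is only the end of a range.

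**The article is condensed.** A rescaling may be described in the full protocol. That the spread is a 25-week spread is indeed inferred from the method as described. The conflict between the printed means needs no such inference.

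A reader might infer that the trial is underpowered. The documents do not support that: there is no 48-week SD, and for a true 50% slowing at the cited rates most of the assumed cases give more than 80%.

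**Conclusion.** The point holds as a mismatch of time scale. A loss observed over 25 weeks (9.1 points) is presented as the one-year loss (9 points), although the section's own rates give 15.9 to 17.5 points at week 48 if decline is linear. The planned 4.5 points would then be a 26 to 28% reduction, not the stated 50%, which would be 7.9 to 8.7 points. The stated 80% power is consequently not established for the primary comparison at week 48.

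The size of the error cannot be reduced to one number. With a pilot SD of 4.2 to 6.1 (which assumes a grid in steps of 30), SD growth of 1.39 to 1.92, two-sided 5% and 30 per arm, power is 83% down to 31% for 4.5 points and above 99% down to 73% for 7.9 to 8.7 points. These ranges are illustrative. The direction of the error is not determined, and neither too little nor too much power has been shown. The numbers screened, randomised and evaluable are consistent with each other, and the endpoint, the analysis model and the type I error are not affected.

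**What to change.** Choose one of two routes and say which.

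1. Put the placebo decline, the 50% effect and the residual SD on a single 48-week scale, give the source of each or an explicit rescaling of the pilot data, and re-run the simulation.
2. State that 4.5 points at week 48, about 26 to 28% of the decline implied by the cited rates, is a deliberately cautious target for this population, and give its power with a 48-week SD.

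In both cases replace the single 80% by a power range with its SD assumptions, state the steps of the size grid and the sidedness of α, and keep 71 randomised.

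The cost is one re-run of existing code and a paragraph of text, with no added patients. The downside is that the reported power may become a wider or less favourable range.
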